### Randomisation/treatment allocation

Random allocation to the postcard group and the control group will be carried out by the independent statistician ([name]), who has no knowledge about participants characteristics, using blocked randomization and computer generated random numbers. This will be concealed from the research team. The statistician will notify the study coordinator regarding the group allocation. The study coordinator will send out the postcards once per month.

The research assistant, who carries out the assessments, will be blind to group allocation. The success of blinding will be assessed at 18-months via questioning the research assistant regarding whether they think the participant received postcards as part of the RCT - Yes/No.

### Statistical methods

At each follow-up time point the general linear model will be used to test for the treatment factor, i.e. to compare the intervention and control groups for each outcome measure. The corresponding baseline values of each outcome measure will be used as the covariate. In addition, the effects of other possible predictors (such as gender and age) on outcome will be explored. Multi-level modeling will be used to compare the trend over time for each outcome in the two groups. Both the last observation carried forward and multiple imputation techniques will be considered if the amount of missing values is substantial.

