### Control intervention

Those in the control group will receive the initial 'sources of help' interview but no postcards.

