### Outcomes

The primary outcomes are suicidal behaviour and ideation, DSH, hopelessness, depression, self-esteem, help-seeking and perceived social support, with assessment at baseline, 12 and 18-months. The acceptability of the intervention will also be assessed by calculating the proportion of participants who choose to discontinue receiving the postcards and via an evaluation questionnaire administered at 12-month follow-up. This questionnaire also asks participants whether or not they had employed any of the help-seeking strategies recommended in the postcards.

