### Sample size calculation: effect size and statistical power

Suicide and SA rates from other studies vary between 3.9% and 15.1% for a contact group, and 4.6% and 17.3% for a non-contact group [11,10], with small effect sizes. The design of our study differs from previous studies and it is not possible to make any firm inference for our study, although it is reasonable to expect a similar effect size. The power analysis for this study is based on using the general linear model to compare the intervention and control groups with the baseline values of an outcome measure as the covariate. It is assumed (conservatively) that the covariate would explain 5% of the variance in the dependent variable. Based on previous research at this centre, we expect to recruit 180 subjects who would be equally allocated to the two groups and conservatively estimated a drop-out rate of 20%. A power calculation indicated that we would be able to detect a small effect size of 0.21 with a significance level of 0.05 and power of 0.8. The actual sample size (n = 165) has made only a small change to the power calculation - the detectable effect size has increased from 0.21 to 0.22.

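### The 18-month treatment test is a separate general linear model that, unless values are imputed, leaves out the month-12 scores of participants lost later; the planned multi-level model could use them

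*Protocol article*

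**What the plan says.** All references are to the Protocol article.

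- Outcomes: every outcome is measured "with assessment at baseline, 12 and 18-months".
- Statistical methods, treatment test: "At each follow-up time point the general linear model will be used to test for the treatment factor". On adjustment: "The corresponding baseline values of each outcome measure will be used as the covariate". The month-12 score is not named as a term in the 18-month model.
- Statistical methods, second model: "Multi-level modeling will be used to compare the trend over time for each outcome in the two groups". No treatment difference at a given visit is asked of it.
- Statistical methods, missing data: "Both the last observation carried forward and multiple imputation techniques will be considered if the amount of missing values is substantial". No threshold is given, and no choice between the two techniques.
- Sample size calculation: "we expect to recruit 180 subjects who would be equally allocated to the two groups", and the authors "conservatively estimated a drop-out rate of 20"%. The loss is not divided by visit or by arm. For power, the baseline covariate is assumed to explain 5% of outcome variance.
- Control intervention: "Those in the control group will receive the initial 'sources of help' interview but no postcards". Under Intervention, the postcards are monthly for 12 months from the month after baseline.

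**The concern.** A general linear model fitted at month 18 uses only people with a month-18 score. Someone assessed at baseline and month 12 and then lost contributes nothing to it, although the month-12 score is probably the best available predictor of the missing value. If baseline explains about 5% of the variance, adjusting for it does little to repair selective loss.

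Suppose that controls who are doing badly at month 12 tend to be the ones lost. The remaining controls then look too well at month 18, and a lasting benefit is understated. If the selection is in the postcard arm instead, the benefit is overstated. The plan already fits, for every outcome, a type of model that could use those month-12 scores, but it gives that model a different question.

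**Working it through.** **1. Effect size used.** The article's detectable effect of 0.21 (0.22 at n = 165) reads as Cohen's f. A two-sided 5% test with 80% power, no covariate and no drop-out, gives f = 0.210 at N = 180 and 0.219 at N = 165. For two equal groups d = 2f, so d = 2 × 0.21 = 0.42. (Applying the stated 20% drop-out and 5% covariate gives f = 0.229 and 0.240. That mismatch is a separate matter and does not affect this point.)

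**2. Inputs.** From the article: 20% loss per arm, and baseline R² of 5%. Assumed, because the article gives no figure: correlation ρ between months 12 and 18 of 0.4, 0.6 or 0.8; how the 20% divides before and after month 12; and how strongly later loss rises with a worse month-12 score (log-odds per SD). Loss before month 12 is taken as random.

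**3. Formula.** Let q be the proportion lost after month 12 among those seen at month 12, and g the gap in SD between the month-12 mean of those lost and that of the whole arm. The month-12 mean of those who remain shifts by q/(1 − q) × g. The bias carried into the baseline-adjusted month-18 mean is about (ρ − 0.05) × that shift. The bias in the treatment difference is the difference of this quantity between arms. For a normal score, log-odds of 1 per SD gives g = 0.80 at q = 0.111 and 0.88 at q = 0.059; log-odds of 0.5 gives g = 0.46 at q = 0.059.

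**4. Results**, per-visit model at month 18, true d = 0.42:

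- A. Selection in controls only (log-odds 1), 10 points lost before and 10 after month 12: q = 0.10/0.90 = 0.111; shift = 0.125 × 0.80 = 0.100. Bias = 0.35, 0.55 or 0.75 × 0.100 = 0.035, 0.055 or 0.075. Understatement: 8%, 13% or 18%. Simulation: 0.39, 0.36, 0.35.
- B. As A, but 15 points before and 5 after: q = 0.05/0.85 = 0.059; shift = 0.0625 × 0.88 = 0.055. Bias = 0.019, 0.030 or 0.041. Understatement: 5%, 7% or 10%. Simulation: 0.40, 0.39, 0.38.
- C. As B, with selection in both arms (log-odds 1 in controls, 0.5 in the postcard arm): shift = 0.0625 × (0.88 − 0.46) = 0.026. Bias = 0.009, 0.014 or 0.020. Understatement: 2%, 3% or 5%. Simulation: 0.41, 0.40, 0.40.

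The model that uses month-12 scores returns about 0.42 throughout, because these data are missing at random by construction.

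**5. Equal selection.** With the same slope and the same loss in both arms the bias is zero, and the gain from the other model is a standard error 1 to 3% smaller. If one identical loss rule acts on both arms and the treatment has already lowered month-12 scores, loss itself becomes unequal. With true d = 0.44, ρ = 0.7, log-odds 1 and all loss after month 12, 15% are lost against 20%, and the understatement is 0.035 (8%).

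**6. Stress case.** True effect zero, n = 165, ρ = 0.7, all 20% lost after month 12. Two-sided type I error of the completer model is 10.8% with selection in one arm and 26.5% with opposite selection in the two arms, against 5.3% and 5.0% when month-12 scores are used. These settings are deliberately severe.

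**7. LOCF.** Also with true effect zero and all loss after month 12, carrying the month-12 score forward left bias of the opposite sign, 0.03 to 0.14 SD.

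**The case against.** **The plan does not simply ignore month-12 scores.** A reader might infer that it does. The multi-level model uses them, and multiple imputation that included them would remove the bias under missing at random. With 20% loss expected, imputation may well be triggered. This stands as a limit on the point. It does not remove it, because the imputation is conditional, the alternative on offer is LOCF, and the treatment test at each visit is assigned to the general linear model.

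**The contact difference does not act when it would need to.** It is tempting to argue that loss will differ by arm because only one arm is contacted between visits. The article does not support that for months 12 to 18: the postcards, each with its change-of-address slip, stop at about month 12. Arm-differing loss afterwards would have to be a carry-over of earlier contact or of the treatment effect. People lost before month 12, when contact does differ, have no month-12 score to recover.

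**The multi-level model is not a guarantee.** It removes the bias only under missing at random. When loss was made to depend on the unseen month-18 score, in the severe setting with all loss after month 12, the likelihood estimate was also biased (0.09 to 0.19 SD, against 0.17 to 0.33 for completers). A comparison of linear trends would not directly give the month-18 difference.

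**Baseline-adjusted analysis at each visit is standard, matches the power basis, and detail may sit in an analysis plan.** True. But the article states which model tests treatment, so this concerns a stated choice and not an omitted detail.

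**Conclusion.** The point holds in a conditional form. As written, and without imputation, the 18-month test throws away month-12 scores that the trial will have collected. If loss between months 12 and 18 depends on those scores differently by arm, the 18-month effect is biased. With true d = 0.42 and 20% loss in each arm, the understatement in controls-worse-lost scenarios is roughly 2 to 18%, depending on how much loss falls after month 12 and how far selection differs. Against a standard error of about 0.17, the largest shift in those scenarios (0.075) is 0.075/0.17 = 0.4 standard errors.

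The correlations, the timing of loss and the selection strengths are assumptions. The documents do not show that such selection will occur or in which direction. Unequal drop-out rates alone, or loss explained by arm and baseline score, would not bias the baseline-adjusted test. The change is worth making because it is cheap, not because bias is established.

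**What to change.** In Statistical methods, take the 12-month and 18-month treatment differences from the multi-level model already planned: baseline value as covariate, visit as a category, treatment-by-visit terms, and every participant with at least one follow-up score. Use the binary version for yes/no outcomes such as the actual help-seeking subscales. An equivalent route is to keep the general linear model and commit to multiple imputation that includes the month-12 score, and not LOCF. Keep the per-visit general linear models as a sensitivity analysis, and state the missing-at-random assumption.

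The cost is a few sentences and slightly more modelling work; no new data or visits are needed. The change does not protect against loss that depends on unseen scores, and it cannot recover people lost before month 12 and never seen again.

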### Participants

Participants will be recruited from OYH triage over a 12 month period. Inclusion criteria are: 15 to 24 years; resident in Northwestern Metropolitan region of Melbourne; refused from service; current or lifetime history of suicidal ideation or attempts or DSH. These will be assessed by a Research Assistant (SG) via the written triage records. Exclusion criteria are: known organic cause for presentation; intellectual disability; inability to speak English. The participant flow chart is shown in Figure 1.

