### Outcome measures

Basic demographic details, including age, gender, employment or educational status, living circumstances, country of birth, parents' or guardians' employment status, parents' or guardians' country of birth, medical history and details of any treatment being received, are recorded on a specifically designed, standardised questionnaire.

Axis-I diagnoses will be assessed using the Structured Clinical Interview for DSM-IV [19].

Depression will be assessed by the Center for Epidemiologic Studies - Depression scale [20] a 20-item measure of current level of depressive symptomatology. A cut off score of 24 was used in this study in order to detect symptoms more likely to be of clinical significance [21].

The Beck Scale for Suicidal Ideation (BSS) [22] measures suicidal ideation and intent. This is a 19 item self-report scale with items rated on a 3-point scale (0-2). The total score ranges from 0 to 38. Higher scores indicate greater suicidal ideation.

The Brief Reason for Living Inventory - Adolescent Version (BRFL-A) [23] is a self-report instrument that assesses suicide ideation and behaviour. Higher scores, as rated on a 6-point scale (1 = not at all important to 6 = extremely important), indicate greater reasons for living.

The Suicidal Behaviours Questionnaire (SBQ-14) [24] measures five domains: past suicidal ideation, future suicidal ideation, past suicide threats, future suicide attempts, and the likelihood of dying in a future suicide attempt. These domains are rated across a number of time points: (1) the past several days including today, (2) past month, (3) past four months, (4) past year, and (5) lifetime. The SBQ-14 also assesses the number of episodes of DSH and suicide intent during the past year. In the present study, this section of the questionnaire was modified to assess lifetime and past month ratings of self-injurious behaviour and suicide intent in order to provide more specific information about chronicity and current risk of suicidal behaviour.

The Beck Hopelessness Scale [25] measures hopelessness. This is a 20-item true-false scale that measures the extent of negative attitudes about the future. A total score is obtained by summing the ratings with a potential scoring range of 0-20. High scores reflect greater hopelessness.

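### Last observation carried forward is left open as a missing-data method, although with visits only at 0, 12 and 18 months it can enter a pre-postcard score as the outcome

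*Protocol article*

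**What the plan says.** The protocol article's Statistical methods section plans a general linear model at each follow-up, comparing the arms on each outcome: "The corresponding baseline values of each outcome measure will be used as the covariate". It adds a longitudinal analysis: "Multi-level modeling will be used to compare the trend over time for each outcome in the two groups". On missing data it has one sentence: "Both the last observation carried forward and multiple imputation techniques will be considered if the amount of missing values is substantial". LOCF and multiple imputation thus stand side by side, and neither is marked as the main method or as a sensitivity analysis.

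Three other statements bear on what LOCF would do here:

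- Outcomes: outcomes are measured "with assessment at baseline, 12 and 18-months", so there is no visit between baseline and month 12.
- Intervention: the postcards begin in the month after the baseline assessment, so every baseline score predates them.
- Sample size calculation: the authors "conservatively estimated a drop-out rate of 20" per cent, with no split by arm and no timing.

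**The concern.** LOCF replaces a missing outcome with the participant's latest earlier value. With these visits there are two cases. Someone lost before month 12 has only the baseline value, so a score from before the first postcard becomes both the 12-month and the 18-month outcome. Someone seen at month 12 but not at month 18 carries the 12-month score, which assumes that the result persists after the postcards have stopped. That is one of the things the 18-month visit can test.

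The recall windows make the first case worse for some measures. The self-harm section of the suicidal behaviours questionnaire was "modified to assess lifetime and past month ratings of self-injurious behaviour and suicide intent". A carried past-month rating describes a month before randomisation, and a carried lifetime rating assumes no new event.

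At stake is the estimated effect of a trial planned around a small one. LOCF can dilute a real effect. If the arms lose participants at different rates, it can also add a difference that is not there or hide one that is. Unequal loss is conceivable because only the postcard arm gets monthly mail with a change-of-address slip, but the article gives no figure for it.

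**Working it through.** **Inputs from the article.** Drop-out 20%; N = 180 planned and 165 actual, in two equal arms; detectable effect 0.21 (0.22 at N = 165); baseline covariate explaining 5% of variance, so r = √0.05 ≈ 0.22; analysis by baseline-adjusted linear model.

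**Assumptions, because the article gives no figure.** Improvement m in the control arm of 0 to 1 SD; drop-out by arm of 20/20, 25/15 or 15/25 (control/postcard, %); all drop-out before month 12 and unrelated to outcome; lower scores better.

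**The plan's own figure.** The article gives no figure for the effect of LOCF. Its detectable effect is used only to fix a scale. A two-sided test at 0.05 with power 0.8 on all recruited participants, ignoring drop-out and covariate, gives Cohen's f = 0.2100 at N = 180 and 0.2194 at N = 165. These match the stated 0.21 and 0.22, so I read 0.21 as f, which is d = 2 × 0.21 = 0.42 SD. With 20% drop-out (144 and 132 analysed) and the 5% covariate included, f is 0.229 and 0.240. That mismatch is a separate matter and does not affect this point.

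**Formula.** Drop-outs keep their baseline score, so their recorded change is 0. Completers change by −m (control) or −(m + δ) (postcard), where δ is the true benefit. With drop-out proportions d_c and d_p, the expected LOCF difference, postcard minus control, is

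−(m + δ)(1 − d_p) + m(1 − d_c) = −δ(1 − d_p) − m(d_c − d_p).

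Randomisation balances the baseline, so adjusting for it leaves this expectation unchanged.

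- Equal 20% drop-out: the second term vanishes and the result is −0.8δ, whatever m is. For δ = 0.42 it is −0.8 × 0.42 = −0.336.
- No true effect: only −m(d_c − d_p) remains. It is 0 if drop-out is equal or m = 0, and −1 × 0.10 = −0.10 SD at 25/15 with m = 1.

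| Drop-out, control/postcard | m (SD) | LOCF, δ = 0 | LOCF, δ = 0.42 |
|---|---|---|---|
| 20/20 | any | 0 | −0.336 |
| 25/15 | 0 | 0 | −0.357 |
| 25/15 | 0.5 | −0.05 | −0.407 |
| 25/15 | 1 | −0.10 | −0.457 |
| 15/25 | 0 | 0 | −0.315 |
| 15/25 | 0.5 | +0.05 | −0.265 |
| 15/25 | 1 | +0.10 | −0.215 |

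Large-sample simulation agreed with each row. The baseline-adjusted analysis of observed cases returned the true value in every scenario. It must do so here, because drop-out was simulated as unrelated to outcome.

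**Error rates at N = 165** (3,000 simulated trials, r² = 0.05):

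- Type I error of LOCF with 20/20 drop-out: 0.047 (m = 0.5) and 0.055 (m = 1), which is nominal.
- Type I error of LOCF with 25/15 drop-out: 0.067 (m = 0.5) and 0.098 (m = 1). Observed cases gave 0.049 and 0.052.
- Power for δ = 0.42 with 20/20 drop-out and m = 0.5: LOCF 0.59, observed cases 0.68.

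**The case against.** The strongest reply is that the article does not commit to LOCF. The method is only to be considered, alongside multiple imputation and only if much is missing. The sentence could mean that both are run as sensitivity analyses. The multi-level model, by contrast, is a firm commitment, so much of the remedy is already in the plan. A threshold for how much missingness counts, and a rule for choosing between methods, are details that an article commonly leaves to the analysis plan.

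Much of this stands. The absence of a threshold or rule is not counted as a fault here, and the multi-level model is a real mitigation. What remains is that the article names a method ill suited to its own visit schedule as a candidate equal to multiple imputation, and nothing in it stops that method from deciding the result.

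A reader might also infer more than the article supports:

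- *That LOCF necessarily biases the comparison.* Its bias depends on drop-out by arm, change over time and the true effect, none of which is given.
- *That baseline is a crisis score bound to fall.* Recruitment is from triage, but eligibility is "current or lifetime history of suicidal ideation or attempts or DSH", and nothing describes the baseline interview as taking place in crisis. Improvement is therefore an assumption, shown as a range.
- *That every drop-out is recorded as unchanged.* Those seen at month 12 carry a score taken during follow-up.
- *That a death by suicide would be given a living participant's baseline score.* The article does not say that deaths would be treated as missing interviews.

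**Conclusion.** The point holds in a conditional form. LOCF is left open, and for anyone lost before month 12 it would use a score from before the postcards as the outcome.

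- **Dilution.** Equal 20% drop-out before month 12 shrinks any true effect by 20%, whatever the scale or the change over time. The power loss, about 0.68 to 0.59, is less general. It also assumes N = 165, 0.21 read as Cohen's f, 5% variance explained, 0.5 SD improvement and drop-out unrelated to outcome.
- **Bias in either direction.** With an assumed 25% v 15% split and 0 to 1 SD improvement, the spurious difference under no effect is 0 to 0.10 SD and type I error about 0.05 to 0.10. Its sign depends on which arm loses more participants. With equal drop-out, or no change over time, there is no bias under no effect.

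This should be changed, but it is not a fatal flaw: LOCF is only one option, and better methods are already named in the same section. Those methods rely on data being missing at random. If drop-out depends on outcomes that were not observed, they too can be biased.

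**What to change.** Remove LOCF as a candidate for the main analysis, or keep it only as a labelled sensitivity analysis. Make the multi-level model already planned the main analysis under missing at random:

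- fit it to all available data;
- treat time as a category (0, 12 and 18 months) and include arm-by-time terms;
- report the difference between arms at both 12 and 18 months.

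Use multiple imputation, done separately by arm, as the supporting analysis. The cost is a change of wording and a little more analysis work. No extra data collection is needed.

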### Safety and supervision

The research assistant received training in the administration of the measures and in the assessment of suicide risk. The research assistant will make contact with the research fellow (JR) overseeing the study once each assessment was complete. If there is no cause for concern, contact will be made via SMS. If there are concerns about the participant, contact will be made by telephone or face-to-face and the concerns will be discussed. If the research fellow is concerned about the participant, an immediate referral will be made to an appropriate service. Additionally, weekly supervision meetings with an experienced clinical psychologist (EC) will be held, during which all cases will be presented and any diagnostic and/or risk issues discussed. Any young people considered to be at elevated risk will be referred to an appropriate service.

